**Fig. 2 Fig2:**

Schematic representation of study design and data collection The green line represents the supplementation period

#### Stool samples

Stool specimens will be collected on four separate occasions: after the first-stage revision surgery (baseline, t0), at four weeks (t4) and eight weeks (t8) post-supplementation. The fourth sample will be collected at the time of second-stage surgery. Participants will be asked to store the specimens in a freezer (sealed in the stool kits provided) and bring them along on the day of the clinical review. All specimens will be stored at -80 °C until further analysis. The modified Gastrointestinal Symptom Rating Scale Questionnaire (mGSRS) will be administered to assess the overall gut symptoms of participants. The mGSRS is a short series of questions about gastrointestinal symptoms. Additional questions about stool frequency (how often), consistency (using Bristol Stool Chart) and perceived normality of bowel habits (Likert scale) are included (supplementary file 2). The gut health survey will be done at baseline (t0) and 8-week time-point (t8). Stool DNA will be extracted per the previously published protocols [35]. Real-time polymerase chain reaction will assess the abundance of known enteric pathogens. Deep sequencing of the DNA will be done to determine the nature of the microbiota. The gut microbiome will be analysed using the R Package, and the abundance of microbes, including phylum, genus and species level, will be correlated with PJI. Faecal inflammation biomarkers, including faecal calprotectin, will be measured with ELISA. Short-chain fatty acids and pH will be measured as published previously [36, 37].

**Table 1 Tab1:**
[figure not shown]
Schedule of enrolment, interventions, and assessments

#### Blood and bone tissue collection

All tissue samples will be taken during the first-stage and second-stage surgeries. Soft tissue, bone, and synovial fluid (when present) will be retrieved intra-operatively using sterile surgical instruments and snap-frozen immediately upon collection. Identifiers will be removed, and the samples will be labelled with the study ID code. During each surgery, 10 ml of venous blood will be collected in SST, heparin and EDTA-coated tubes intraoperatively. The specimens will be processed, split in Eppendorf tubes and snap-frozen at -80 °C until further analysis. The plasma and serum specimens will be analysed for inflammatory markers, including interleukins (IL-1, IL-6 and IL-10), C-reactive protein (CRP), erythrocyte sedimentation rate (ESR), albumin, CD4/CD8, CD14, lipopolysaccharides (LPS), Zonulin and tumour necrosis factor-alpha (TNF-alpha) using validated ELISA assays. Blood DNA will be extracted from whole blood, and deep sequencing of the DNA will be done to determine the nature of the microbiota [38]. The blood microbiome will be analysed using the R Package, and the abundance of microbes, including phylum, genus and species level will be compared between the groups.

#### Dietary pattern

Patients’ dietary patterns at baseline will be collected using a food frequency questionnaire screener (FFS) validated for the Australian population and a 4-day Food Diary by the study dietitian (AM). The patients who habitually consume a higher-fibre diet may have a significantly different microbiome profile than those who consume a lower-fibre diet. Hence, this tool will allow us to identify the added effect of prebiotic fibre.

#### Patient data

The participant’s medical records will be accessed to extract information on previous total joint replacement, demographics, medical and surgical history, physical examination, laboratory investigations, medical imaging, operative reports, and readmission due to infection and surgical complications. This information is a part of the standard of care protocol for any PJI patient, independent of study participation.

#### Assessment of treatment outcomes based on the Delphi criterion

The longer-term outcome of this study will be to investigate treatment success based on the Delphi criterion for PJI following second-stage revision surgery. The Delphi group treatment success is based on three critical dimensions: (1) eradication of infection, (2) no subsequent surgical intervention, and (3) no mortality related to PJI (supplementary file 1) [33]. The time point followed will be one and two years after the second stage of surgery.

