#### Study Design and products

In this 8-week, single-centre, double-blind, randomised controlled trial, 80 patients scheduled to undergo two-stage revision surgery for the treatment of PJI will be randomised to receive resistant starch or a placebo containing corn starch. The test product is a commercially available ready-to-mix beverage powder rich in resistant starch (34 g high amylose corn starch, RS2, per serve) available in the Australian market. Patients in the intervention group will receive one sachet of the test product, and those in the placebo group will receive an equivalent amount of ready-to-mix corn-based custard powder for eight weeks. The test and the placebo products will be procured from the market and re-packed in unlabelled plain sachets in a Food Standards Australia New Zealand (FSANZ) approved facility. The treating surgeons will recruit the participants when they present to the Department of Orthopaedics and Trauma for PJI treatment. All patients will be followed up at 2, 4 and 8 weeks after first stage revision and one and two years after the second-stage revision. The study flowchart is shown in Fig. 1.

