### Treatment allocation, randomisation and blinding

Patients who consent to participate will be enrolled in the study and assigned a code. Once enrolled, all patients will undergo standard-of-care treatment for their PJI, including optimisation by a multidisciplinary team comprising an anaesthetist, infectious diseases consultant, orthopaedic doctors, joint replacement nurses, dietitian, and post-surgical antibiotic therapy. Using a computer-generated block randomisation plan, one study investigator will randomly assign the patients to the placebo or intervention group. The treating surgeon and the patient will be blinded to the treatment allocation. Supplementation will start soon after the first-stage revision surgery when the patient is well enough to take oral foods. Based on the randomisation plan, the recruited patients will receive one sachet of test or control product mixed with milk, juice or food of their choice once a day for eight weeks. All in-patients will get the product with breakfast, supervised by the study dietitian. On discharge, patients will be given the clinical supplies to complete the supplementation daily for eight weeks. One of the investigators will ensure compliance through regular phone calls.

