### Outcomes measures

Primary outcome: The primary outcome is the change in gut microflora between the placebo and the test group after 8 weeks of supplementation.

Secondary outcomes: The study has several secondary outcomes, which are listed below:

Change in faecal calprotectin and short-chain fatty acids within and between cohorts at the end of 8-week supplementation.Change in Interleukin levels (IL-1, IL-6 and IL-10) within and between cohorts at the end of 8-week supplementation.Changes in C-reactive protein, CD4 and zonulin levels within and between the placebo and the test group at the end of 8-week supplementation.Tissue microbiology results will be compared between cohorts during first and second-stage surgery.Treatment outcomes using the Delphi criterion [33] (supplementary file 1) will be reported for the two cohorts at one and two years after second-stage surgery.

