To our knowledge, only one clinical study has investigated gut dysbiosis directly in PJI patients. This recent study reported significantly (*p* < 0.001) higher levels of Zonulin, a marker of increased gut-permeability, in PJI patients (7.6 ± 6.1 ng/ml) as compared to primary arthroplasty patients (3.9 ± 4.5 ng/ml) [40]. While this study used surrogate markers of gut permeability, pilot data generated at our hospital (unpublished) suggests the existence of gut dysbiosis in PJI patients. In the current study, we will administer resistant starch or placebo to PJI patients for eight weeks and investigate the changes in the gut microbiome. In addition, an array of plasma inflammatory and gut permeability markers and blood microbiomes will be measured. Apart from directly assessing gut dysbiosis, this study will also evaluate if the dysbiosis can be reset through prebiotic intervention.

There are some limitations in the design of this study. Firstly, this is a single-centre study with an estimated sample size. It is clinically and ethically essential to generate proof of concept data before any large-scale interventions can be planned. If the results from this initial study are promising, we will undertake a multicentre study to validate the findings. Secondly, the impact of change in gut microbiome on surgical outcomes will be evaluated one and two years after the second stage revision. Due to the nature of PJI, many patients may not be able to make it to the longer-term follow-up either due to premature death or non-resolution of infection, thus requiring several repeat first-stage surgeries, or may not be medically fit to undergo second-stage revision due to comorbidities. Lastly, the patients will take the product at home (after discharge) and administer the intervention products. To encourage compliance, one of the study investigators will phone the patients regularly and empty packages will be returned to investigators.

In conclusion, this study’s findings will provide the first clinical evidence of targeting gut health to prevent and manage joint infections.

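### The secondary Delphi treatment-success outcome is timed only from second-stage surgery, so randomised patients who do not reach that stage have no defined assessment time

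*Protocol article*

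**What the plan says.** Under Treatment allocation, randomisation and blinding, the protocol article places the start of the intervention between the two operations: "Supplementation will start soon after the first-stage revision surgery when the patient is well enough to take oral foods".

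The clinical outcome starts later. Outcomes measures lists Delphi treatment outcomes last among the secondary outcomes; they "will be reported for the two cohorts at one and two years after second-stage surgery". The section on the Delphi criterion gives the aim as to "investigate treatment success based on the Delphi criterion for PJI following second-stage revision surgery" and adds: "The time point followed will be one and two years after the second stage of surgery". The visit schedule in Study Design and products agrees: the early visits, at weeks 2, 4 and 8, are counted from the first stage, and the one-year and two-year visits from the second. The text describes no visit after week 8 that is counted from randomisation or from the first stage.

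Success rests on three dimensions: "1) eradication of infection, (2) no subsequent surgical intervention, and (3) no mortality related to PJI".

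The limitations paragraph of the Discussion acknowledges that "many patients may not be able to make it to the longer-term follow-up either due to premature death or non-resolution of infection", the latter leading to repeat first-stage operations, and that others "may not be medically fit to undergo second-stage revision due to comorbidities". It gives no rate and no rule for classifying these patients.

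**The concern.** Whether a patient reaches the second stage is settled after randomisation and depends partly on how the infection responds, which is what the supplement is hoped to influence. An outcome that can be assessed only in patients who reach that stage compares two selected subgroups, not the two randomised groups.

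Some of the patients left without an assessment time are also those with the clearest poor results. Infection that has not resolved fails the first Delphi dimension, and PJI-related death fails the third, whether or not a second stage took place.

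This is the only clinical treatment-success measure in the outcome list. Surgical outcomes are in the trial's title and treatment outcomes are in its hypothesis, so the measure will carry whatever clinical message the trial sends.

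**Working it through.** The plan states no figure for this outcome, so there is none to reproduce. The check has two parts.

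**1. Who has an assessment time?**
- Patient has the second stage: assessed one and two years later.
- Patient remains infected and has repeat first-stage surgery without reaching the second stage: non-success on eradication, no assessment time.
- Patient dies of PJI before the second stage: non-success on mortality, no assessment time.
- Patient dies of another cause before the second stage: not non-success on the mortality dimension as quoted, no assessment time.
- Patient is unfit for the second stage because of comorbidity: fails none of the three dimensions on its face, no assessment time.

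**2. How large could the effect be?** Inputs:
- S, true success among all randomised patients: 54% in both arms. This is an assumption, taken as 100% − 46% from the 24-month failure rate cited in the background section.
- q, share not reaching stage two: assumed, because the documents give no rate.
- r, share of those patients who would count as successes: assumed.
- c, success among those reaching stage two.

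Since S = (1 − q) × c + q × r, it follows that c = (S − q × r) / (1 − q).

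With r = 0 (no patient who misses stage two is a success):
- q = 10%: 0.54 / 0.90 = 60.0%
- q = 20%: 0.54 / 0.80 = 67.5%
- q = 30%: 0.54 / 0.70 = 77.1%

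So 10% v 20% produces a false gap of 7.5 points, and 10% v 30% a false gap of 17.1 points. Each favours the arm that lost more patients.

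With r = 27% (half of S), for 10% v 20%:
- (0.54 − 0.027) / 0.90 = 57.0%
- (0.54 − 0.054) / 0.80 = 60.75%
- gap 3.75 points

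With r = 54% both rates return to 54% and the gap is zero.

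If q is equal in the two arms (and r and S are too), no false gap arises. The level is still overstated when r = 0, by a factor of 1 / (1 − q): 1.11 at 10%, 1.25 at 20%, 1.43 at 30%.

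**Context.** With 80 patients split 40 per arm (1:1 is assumed) and 54% success, the standard error of the difference is √(2 × 0.54 × 0.46 / 40) = 0.111. The 95% half-width is 1.96 × 0.111, about 22 points. The illustrated bias lies within the random error of a trial this size, but a confidence interval would not reveal it.

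**The case against.** The strongest reply is that a reader might infer from the time origin that the plan removes these patients from the denominator, and no sentence says so. The Delphi section fixes when success is assessed; it does not define the denominator. Results are promised for both cohorts, the full Delphi definition is in a supplementary file that is not shown, and an analysis plan could supply the handling. That stands as a limit on the claim. It does not remove the problem, because the time origin and the visit schedule are stated rules, and under them these patients have no assessment time.

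Four other stronger readings fail:
- That many patients will not reach stage two. The Discussion says they may not, gives no rate, and speaks of longer-term follow-up. Some of the deaths could come after the second stage.
- That everyone who misses stage two is a failure. Only PJI-related death counts on the mortality dimension as quoted, and unfitness from comorbidity is not a failure on its face.
- That harm before stage two would go unseen. The Patient data section extracts operative reports and infection readmissions without restricting them to the period after the second stage, and adverse events are to be recorded.
- That the trial's main result is compromised. The primary outcome is the microbiome at 8 weeks, the sample size was set on beta diversity, and the study is presented as proof of concept.

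It is also fair to say that success after reimplantation is a legitimate question and that the authors disclose the attrition. Disclosure does not supply a counting rule, and the question about reimplanted patients can be kept alongside one that respects randomisation.

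**Conclusion.** The concern holds as a correctable weakness in a secondary outcome. As written, Delphi success can be assessed only in patients who reach a post-randomisation event, and the comparison between arms is biased if the proportion reaching it differs. The size cannot be derived from the documents. The 7.5-point example rests on assumed values: 54% true success in both arms, 10% v 20% not reaching stage two, and none of those patients a success. It shrinks as more of them would count as successes and vanishes if the arms lose equal shares under the same assumptions. The documents do not show that the arms will differ, and they do not state that anyone is excluded on this ground. The primary analysis is not touched. The change is still worth making, because it is cheap and this is the only clinical success measure listed.

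**What to change.** Add to the outcome definition a Delphi-based analysis of all randomised patients at fixed times from randomisation or first-stage surgery.

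- Count persistent infection and PJI-related death before stage two as non-success.
- Word the surgical dimension so that the planned second stage does not itself count as a subsequent intervention, and say how repeat first-stage surgery is classified.
- Prespecify the handling of unrelated deaths and of patients unfit for stage two, for example as a competing event, with a sensitivity analysis that counts them as failures.
- Report the proportion reaching stage two by arm.
- Give the risk difference with a 95% confidence interval.
- Keep the rate timed from the second stage as a descriptive result.

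The cost is a little more chart review at fixed dates, using records that the Patient data section already plans to extract. The drawback is that follow-up after reimplantation will be of unequal length within a fixed window. The text shown states no interval between the stages, so the window has to be chosen with that in mind.

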### Adverse outcomes

Patients will be instructed to inform the researchers about any changes or discomfort experienced with the products. However, they will be counselled to help understand normal expectations when starting a prebiotic, e.g., flatulence for a few days. Furthermore, during follow-up visits, the researchers will ask about adverse events which may be related to the intervention. Adverse events, if any, will be recorded and reported in publication. The likelihood of adverse events after administering the test or placebo products is negligible, as both are well-established in-market products.

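### The adverse event enquiry is worded around presumed relatedness to the product, so unexpected or unattributed events during supplementation can be missed

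*Protocol article*

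**What the plan says.** The Adverse outcomes section of the protocol article describes two routes by which an adverse event becomes known.

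- Spontaneous: "Patients will be instructed to inform the researchers about any changes or discomfort experienced with the products". The next sentence adds that "they will be counselled to help understand normal expectations when starting a prebiotic, e.g., flatulence for a few days".
- Solicited: at the follow-up visits, "the researchers will ask about adverse events which may be related to the intervention".

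It then states that "Adverse events, if any, will be recorded and reported in publication", and closes with an expectation: "The likelihood of adverse events after administering the test or placebo products is negligible", on the ground that both products are already on the market.

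Other sections collect harm-type information without calling it adverse event data. Stool samples provides for a gut symptom questionnaire (mGSRS, with stool frequency and consistency) at baseline and week 8. Patient data provides for extraction from medical records, including "readmission due to infection and surgical complications". The section on the Delphi criterion covers infection eradication, further surgery and PJI-related death at one and two years after second-stage surgery.

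**The concern.** In a randomised, placebo-controlled trial, the difference between arms is the best evidence on whether an event is caused by the product. That works only if events are gathered the same way in both arms, with no prior view about cause. Here the visit question is framed by possible relatedness and the spontaneous route by association with the product. An event that neither the patient nor the researcher connects with a food supplement need not enter the log, even if it turns out to be more frequent in one arm.

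The harms most exposed are the unexpected ones, because nobody would think to attribute them. The patients have just had first-stage revision for infection and are on post-surgical antibiotics, so many symptoms have an obvious alternative explanation and are easily set aside as unrelated. A short list of related events at the end of the trial would then partly reflect how the question was put.

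**Working it through.** No arithmetic applies. The article states no adverse event rate, no safety sample size and no between-arm safety test. The check is a side-by-side reading of every place in the article that collects harm-type information, asking whether entry depends on a presumed link to the product and what is left uncovered.

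| Source (section) | Depends on a presumed link to the product? | What it leaves uncovered |
|---|---|---|
| Visit question (Adverse outcomes) | Yes, framed by possible relatedness | Events not thought to be related |
| Patient reports (Adverse outcomes) | Yes, tied to the products | Events the patient attributes to surgery, infection, antibiotics or nothing in particular |
| mGSRS and stool questions (Stool samples) | No | Non-gut events; possibly gut symptoms that appear and resolve between baseline and week 8 |
| Record extraction (Patient data) | No | Events that lead to neither readmission for infection nor a surgical complication |
| Delphi outcomes (Assessment of treatment outcomes) | No | The supplementation period; anything other than infection control, reoperation and PJI-related death |

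Step by step:

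1. The adverse event log is fed by the first two rows, and both carry the condition. The recording sentence is not itself restricted by cause, but it can apply only to events that have come to light.
2. No section says that events are collected regardless of cause and assessed for relatedness afterwards.
3. The last three rows carry no such condition, so the filter applies to the adverse event log and not to all harm-type data.
4. What no row covers without the filter is a non-gut, non-surgical, non-infectious event during the eight weeks of supplementation. A transient gut symptom between the two questionnaires may also be missed. How far week 8 answers reach back depends on the questionnaire's recall period, which the article does not give.
5. The contacts needed to close the gap already exist. Study Design and products schedules visits at 2, 4 and 8 weeks after the first stage, and the section on treatment allocation provides for regular compliance phone calls.

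Two further passages bear on the remedy. The section on allocation and blinding names the surgeon and the patient as blinded and has one investigator assign the groups; it does not say whether the researchers who ask about adverse events are blinded. Data collection excludes from the final analyses anyone who stops the protocol or takes less than 80% of the product. If that rule were applied to harms, patients who stopped through intolerance would drop out of the report. The article does not say that it applies there.

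**The case against.** The strongest reply is that the wording is mild and the gap narrow. A possible link is a low threshold, there are two routes rather than one, and the recording sentence carries no restriction. The harms of most concern in these patients, namely recurrent infection, reoperation and surgical complications, are caught from records and through the Delphi outcomes whatever anyone thinks of the product. Gut intolerance, the most plausible product effect, is scored at baseline and week 8. All of this stands, and it limits the point to other events and transient symptoms during supplementation. It does not remove the condition from either route into the log.

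A reader might go further in four ways that the document does not support.

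- That no harm data are collected free of a causality filter. Three sources are.
- That the counselling on expected symptoms discourages reporting. The text offers it as help in understanding what is usual, directly after telling patients to report. A higher reporting threshold is possible, but it is inference.
- That the loss can be put as a figure for reduced power. The rates would have to be invented for a test the article does not plan. A relatedness filter would also tend to keep suspected product effects and drop background events, so a uniform loss cannot be assumed.
- That the article commits to recommending the supplement on these results alone. The abstract's statement is conditional on benefit, and the Discussion calls this proof of concept, with a multicentre study to follow if results are promising.

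Nor is it a fault that the article does not label the symptom scores or readmissions as safety outcomes. A condensed article may leave that to the full protocol.

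**Conclusion.** The point holds as a weakness in how adverse events are ascertained. It rests on a stated rule, so it does not depend on what a fuller protocol or analysis plan might add by way of detail. Followed as written, the adverse event log is filtered by presumed cause before the arms are compared, and unexpected or unattributed events during the eight weeks of supplementation can be missed in either arm.

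The size cannot be stated from the document. The conclusion assumes only that staff ask the question as it is worded and that patients report what the instruction asks for. The primary outcome and the listed secondary outcomes are untouched. What is affected is how much reassurance the published harms report can give. Events not asked about at the time may not be recoverable later.

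**What to change.** Reword the Adverse outcomes section so that, at every planned visit and phone call:

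- all patients in both arms are asked the same open question about any adverse event or change in health since the last contact;
- every event is recorded regardless of suspected cause;
- relatedness is judged afterwards by someone blinded to allocation.

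Report all events by randomised arm for everyone who took any product, whatever their compliance. Place them alongside the change in mGSRS from baseline to week 8 and the readmissions and surgical complications already collected.

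The cost is a change of wording and one short standard question at contacts already in the schedule. The small downside is that more unrelated post-surgical events will have to be logged. No added visit or specimen is needed.
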